#### Power analyses and sample size considerations

3.8.3

Effect sizes yielding 80% power were estimated based on a sample size of 60 subjects, and assuming a type 1 error rate of α = .05, and assuming a sphericity correction of ε = 0.75 for 2 *df* mixed ANOVA models, and an average correlation between all repeated measures of *r* = .5 for all models. Tests of the overall 2x3 mixed ANOVA interaction achieved 80% power at an f-ratio effect size of *f* = 0.184 (i.e., partial η2 = .0327), and interaction tests of contrasts of pairs of times had 80% power for effect size *f* = 0.184 (i.e., pη2 = .0327). ANCOVA models include baseline as a covariate and predict subsequent outcome variance. With respect to predictions at a single post-baseline assessment, 80% power is present to detect an effect size of partial *f* = 0.368 (i.e., pη2 = .119). Both detectable effect size estimates rely strongly on assumptions about error structure. The pilot data will provide new error structure information (within the context of the models above) that will improve future power estimates for a broader RCT. Although this study is not adequately powered to detect small effects, we will generate data sufficient to better inform future power analyses with respect to error structure and effect sizes.

Consistent with NIH guidance for R34 pilot and feasibility studies, the sample size was selected to evaluate feasibility, acceptability, recruitment procedures, and preliminary signals of effect, rather than to definitively test efficacy. Accordingly, the effect sizes reported above reflect the minimum effects detectable at the predetermined feasibility-based sample size, not the effects the current study is powered to confirm. Age stratification (5–9, 10–13, and 14–17 years) will be used to maintain balance on a clinically important developmental variable while preserving the overall sample size. Because the study is not powered to detect age-stratum-specific effects, age will be examined descriptively and included as a covariate in exploratory sensitivity analyses. Pilot data, including stratum-specific variance and correlation estimates, will be used to refine sample size estimates for the subsequent definitive RCT.

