#### Measures

2.2.4

*Feasibility and Acceptability.* Feasibility and acceptability are the primary outcomes for the open trial. Participants will complete a Post-session Questionnaire following each FN + session. This questionnaire was designed to assess the utility and relevance of session content and materials. In addition, the family navigator asks participants about the skills or resources the participant used the previous week. Parent attendance and drop-out will serve as indicators of program acceptability; recruitment feasibility will be measured as the ability to recruit the intended population. Following the 5-week intervention, participants will also complete the Client Satisfaction Questionnaire (CSQ-8) [27]. The CSQ-8 assesses participant satisfaction with the services received including the overall quality, their perception of whether the program met their needs, amount of help received, and the extent to which FN + helped them navigate their child's mental health needs more effectively. The CSQ-8 demonstrates good internal consistency, test-retest reliability, and is sensitive to treatment effects [29].

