### Participants

3.3

Participants (*N* = 60) will be recruited from community agencies that serve or license foster parents in the state of Illinois, social media, and word of mouth. Inclusion criteria are the same as the open trial.

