#### Primary outcome

3.8.1

The primary outcome for this study is parent activation. We will examine change in foster parent activation on the P-PAM-MH from baseline to subsequent time points in the intervention, relative to the attention control condition. Foster parent activation will be measured using the P-PAM-MH. Data will be analyzed using two parallel analytic methods: (1) a 2 (Condition) x 3 (Time) repeated measures ANOVA, and (2) a corresponding 2 x 2 repeated measures ANCOVA (using Baseline as a covariate). The ANOVA model evaluates contrasts in actual outcomes, and the ANCOVA model evaluates adjusted mean contrasts, statistically equating groups on baseline status (thus correcting possible group differences at Baseline, and as is often the case, increasing statistical power using baseline as a covariate). We will conduct preliminary analyses to test for additional covariates such as level of education. For the ANOVA model, in addition to time (*df* = 2) and group by time effects (*df* = 2), pairwise contrasts of outcomes at the 3 times will be conducted on the time factor. In addition to overall treatment group effects, treatment groups will be contrasted on average P-PAM-MH within times, and on change between Baseline and the two post-baseline time points. For the ANCOVA models, groups will be contrasted on the adjusted mean average across all times, on adjusted means at each post-baseline time, and on the difference between the 2 post-baseline adjusted means.

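### The named repeated-measures ANOVA and ANCOVA, in classical form, use only parents with every visit, and the detectable effects assume all 60 recruited are complete

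*Protocol article*

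**What the plan says.** Section 3.8.1 analyses foster parent activation (P-PAM-MH) by "a 2 (Condition) x 3 (Time) repeated measures ANOVA" and by a parallel 2x2 repeated-measures ANCOVA with baseline as covariate. Section 3.8.2 applies the same models to the continuous BTPS outcomes. Outcomes are assessed after the 5-week intervention and at 3 months (section 3.1).

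Section 3.8.3 says: "Effect sizes yielding 80% power were estimated based on a sample size of 60 subjects". Alpha is set at .05, the repeated measures are taken to correlate at .5 on average, and the sphericity input reads: "assuming a sphericity correction of ε = 0.75 for 2 *df* mixed ANOVA models". The 2x3 interaction "achieved 80% power at an f-ratio effect size of *f* = 0.184". The same f is given for interaction contrasts of pairs of times, and partial f = 0.368 for an ANCOVA at one post-baseline assessment.

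Section 3.3 says: "Participants (*N* = 60) will be recruited from community agencies". Loss is foreseen. Section 2.2.4, whose measures section 3.6 carries into the randomised trial, says: "Parent attendance and drop-out will serve as indicators of program acceptability". Section 2.2.6 has the monitoring board review withdrawals. No attrition rate is given.

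**The concern.** The sphericity correction in section 3.8.3 belongs to classical repeated-measures ANOVA; a likelihood-based mixed model does not use one. The classical model needs a complete set of visits from each participant. The 2x3 ANOVA needs baseline, 5 weeks and 3 months, and the 2x2 ANCOVA needs baseline and both later visits. A parent seen at 5 weeks but not at 3 months therefore leaves both models, and a 5-week score already in hand goes unused.

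Two things are at stake. The first is the 5-week comparison, which comes to depend on who returns at 3 months and so departs from the randomised comparison. The second is the detectable effects. They are computed for the number recruited, so any incomplete participant makes them too favourable for the models named. The pilot's variance and correlation estimates are also meant to inform the sample size of the later definitive trial, and estimates from completers alone would carry forward.

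**Working it through.** **Inputs (sections 3.8.3 and 3.4).** N = 60, k = 2 arms at 1:1, alpha = 0.05, correlation rho = 0.5, sphericity eps = 0.75 for the three-visit test. Power comes from the noncentral F distribution.

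**Formulas.**
- Condition-by-time interaction with m visits: lambda = f² × N × m × eps / (1 − rho), df1 = (k − 1)(m − 1) × eps, df2 = (N − k)(m − 1) × eps.
- ANCOVA at one visit: lambda = f² × N, df = 1 and N − 3.
- Partial eta squared = f² / (1 + f²).

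**Reproducing the stated figures at N = 60.**
- 2x3 interaction, m = 3: lambda = 0.184² × 60 × 3 × 0.75 / 0.5 = 9.14, df = 1.5 and 87, power 80.2%. Solving for 80% gives f = 0.1836.
- Pairs of times, m = 2, eps = 1: lambda = 0.184² × 60 × 2 / 0.5 = 8.13, df = 1 and 58, power 80.0%. Solved f = 0.1839.
- ANCOVA: lambda = 0.368² × 60 = 8.13, df = 1 and 57, power 80.0%. Solved f = 0.3679.
- Partial eta squared: 0.0339 / 1.0339 = .0327 and 0.1354 / 1.1354 = .119.

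All stated figures reproduce, with 60 complete participants.

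**Allowing for incomplete participants.** The share missing at least one visit is an assumption. N is replaced by the number of complete cases.

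| Assumed incomplete | Complete cases | Power, 2x3 at f = 0.184 | Power, pairs of times at f = 0.184 | Power, ANCOVA at f = 0.368 | f for 80% power, 2x3 | f for 80% power, ANCOVA |
|---|---|---|---|---|---|---|
| 0% | 60 | 80.2% | 80.0% | 80.0% | 0.184 | 0.368 |
| 5% | 57 | 78.0% | 77.9% | 77.9% | 0.189 | 0.378 |
| 10% | 54 | 75.6% | 75.6% | 75.6% | 0.194 | 0.389 |
| 20% | 48 | 70.2% | 70.4% | 70.4% | 0.206 | 0.413 |
| 30% | 42 | 63.9% | 64.3% | 64.3% | 0.221 | 0.443 |

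For an ANCOVA fitted at one visit, the share to use is that missing the visit in question (or baseline), not the share missing any visit.

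**Can the 5-week contrast be biased?** A large simulation (400,000 participants per scenario) assumed unit variances, all correlations 0.5 and a true effect of 0.50 SD. All 5-week scores were observed. Except under random loss, the chance of missing 3 months depended on the 5-week score. The baseline-adjusted 5-week effect was:

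| Assumed pattern of 3-month loss | Share lost | Completers only | All 5-week scores |
|---|---|---|---|
| Random in both arms | 20% | 0.50 | 0.50 |
| Low scorers lost in both arms | 19% | 0.46 | 0.50 |
| Low scorers lost in FN+, random loss in control | 18% | 0.61 | 0.50 |
| High scorers lost in FN+, low scorers in control (extreme) | 26% | 0.16 | 0.50 |

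The last column is 0.50 by construction, since no 5-week score is missing. Loss before the 5-week assessment would remove that score under any method.

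**The case against.** **Listwise deletion is not written down.** A reader might infer that the plan orders the exclusion of incomplete participants. It does not. The article is silent on incomplete cases, and a condensed article may leave that to a fuller document. This stands as a limit: the loss is a property of the named models in classical form. It does not remove the point, because the models themselves are fixed in section 3.8.1, and a fuller plan that used a mixed model would be replacing them. Imputation could reduce bias but would not restore the power of 60 complete cases.

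**The power figures are not wrong.** A reader might also infer that section 3.8.3 miscalculates power or promises 80% and fails to deliver it. Neither is supported. The figures reproduce, are labelled as based on 60, and are described as minimum detectable effects at a size chosen for feasibility, not as effects the trial sets out to confirm. That lowers the consequence. What remains is that the stated minima are too small for these models once anyone is incomplete.

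**The single-visit ANCOVA may lose fewer.** If it is fitted visit by visit, a parent who misses only 3 months stays in the 5-week analysis. This stands, and it limits how the ANCOVA column is read.

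**Rate and direction are assumed.** Drop-out from the programme is not the same as a missed assessment, and no rate is given. At 5% the shortfall is only about 2 points. Nor do the documents support saying that the FN+ effect would be inflated: the simulated patterns go both ways, and random loss gives no bias.

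**Conclusion.** The concern holds in a limited form. As named, the primary models in classical form discard observed 5-week scores from parents who miss only the 3-month visit. The 5-week contrast is then unbiased but less precise if loss is random, and can be biased upward or downward if loss is related to outcome. The detectable effects are correct for 60 complete participants, but recruiting exactly 60 leaves no allowance for foreseen loss. At an assumed 10 to 30% incomplete, complete-case power at the stated effects is about 76 to 64%.

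These sizes rest on the assumed share incomplete, on the section's own correlation and sphericity values, and on classical fitting with no further handling of missing visits. With every visit observed, the stated figures stand. For a feasibility pilot this is worth correcting but does not undermine the design.

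**What to change.** In section 3.8.1, make the primary analysis a likelihood-based mixed model for repeated measures on all randomised participants as assigned. Use every observed post-baseline score, with baseline as covariate and arm-by-time terms. State that it relies on a missing-at-random assumption. Apply the same change to the continuous secondary outcomes in section 3.8.2.

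In section 3.8.3, keep the N = 60 figures and add the minimum detectable effects over a plausible range of analysable N, for example the 54, 48 and 42 rows above. Label them as complete-case and therefore conservative values. They are not the detectable effects of the mixed model, which also uses partly observed participants.

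Enrolment, visits and data collection do not change. The cost is analysis wording and a slightly less favourable stated detectable effect.

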## Discussion

4

This study seeks to address a critical and persistent gap in the mental health care of youth in foster care by targeting parent activation and barriers to treatment engagement. Given the high burden of psychiatric morbidity and the well-documented delays and disparities in accessing evidence-based treatment, interventions that strengthen caregivers’ capacity to recognize needs, navigate systems, and sustain engagement in care are urgently needed. By adapting a family navigation model to the unique structural constraints of child welfare and delivering it via telehealth to enhance accessibility, FN + seeks to reduce practical barriers while building durable caregiver skills. The phased development approach—including stakeholder-informed refinement, open and randomized-controlled trials—positions this study to generate preliminary evidence regarding feasibility, acceptability, and potential efficacy. If FN + demonstrates improvements in foster parent activation, it may represent a scalable, systems-aligned strategy to promote earlier intervention, reduce placement instability linked to unmanaged behavioral health needs, and ultimately mitigate long-term psychiatric risk among youth in care.

## Data Availability

No data was used for the research described in the article.
